### Interim analyses {21b}

Descriptive statistics will be used to describe the general status characteristics of patients in detail at baseline, such as gender, age, disease course, and stroke risk factors. Mann-Whitney U test will be used to analyse value changes of FMA, NIHSS, MAS, and BI scores among the groups. Repeated measures analysis of variance (ANOVA) will be used to analyse value changes of FMA, NIHSS, MAS, and BI scores across five testing time points (weeks 0, 2, 4, 8, and 12). Adverse events will be summarised with descriptive statistics.

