### Sample size {14}

The primary efficacy parameter is the change in the FMA score from baseline to 3 months after the treatment [31]. According to our preliminary test and a previous study, the primary efficacy parameter (FMA score) of the control group (rehabilitation treatment) will increase by 12.11 points and that of the treatment group (scalp acupuncture combination rehabilitation treatment) will increase by 25.82 points. The FMA average standard deviation is expected to be approximately 4. Considering a one-sided 5% significance level, 80% power and the above data (*μ*_1_ = 25.82, *μ*_2_ = 12.11, *σ* = 4, *α* = 0.025, 1–*β* = 0.8), according to NCSS-PASS V20.0.3 software (https://www.ncss.com/software/pass/), approximately 86 participants will be required in each group to achieve a sufficient sample size. Accounting for a dropout rate of 20%, each group must include 104 initial participants. Therefore, we plan to include a total of 208 participants divided equally into two groups.

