## Statistical methods

### Statistical methods for primary and secondary outcomes {20a}

All analyses will be carried out using IBM SPSS Statistics for Windows, version 22.0 (IBM Corp., Armonk, NY, USA). The measurement data will be expressed as the mean ± standard deviation values. For the outcome measures, the changes in each score and differences between the two groups will be evaluated. Normally distributed data will be analysed using a *t* test, and the non-normally distributed data will be analysed by a rank-sum test. An independent *t* test or rank-sum test will be performed to assess the differences between the two groups. In addition, the count data will be expressed by frequency and analysed by a chi-square test.

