### Composition of the data monitoring committee, its role and reporting structure {21a}

The data monitoring committee (DMC) was established before the study, is independent of the sponsor and has no competing interests. The committee trains researchers on data management. DMC ensures and monitors the quality and completeness of the recorded data.

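### Sections {20a} and {21b} prescribe different tests for the same between-arm comparison of FMA change, and the second set stands under an interim heading although it reads as final analysis

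*Protocol article*

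**What the plan says.** The primary variable is fixed in the protocol article, section Sample size {14}: "The primary efficacy parameter is the change in the FMA score from baseline to 3 months after the treatment". Three statements then say how it will be tested.

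- Section {20a} makes the test depend on the distribution: a t test for normal data, while "the non-normally distributed data will be analysed by a rank-sum test". For the between-group comparison it repeats the alternative, saying that an independent t "test or rank-sum test will be performed to assess the differences between the two groups".
- Section {21b} sets no condition: "Mann-Whitney U test will be used to analyse value changes of FMA, NIHSS, MAS, and BI scores among the groups".
- Section {21b} continues: "Repeated measures analysis of variance (ANOVA) will be used to analyse value changes" in the same four scales, over five times that include week 0.

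Section {21b} carries the heading for interim analyses. Its content is a description of baseline characteristics, the two methods above and a summary of adverse events. It gives no timing, number of looks, boundary or division of alpha. In section {21a} the data monitoring committee trains researchers, and "DMC ensures and monitors the quality and completeness of the recorded data". No review of interim efficacy results is assigned to it.

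**The concern.** Taken together, the sections offer more than one analysis of the same primary variable and do not say which one decides the trial. The trial is open-label, with only assessors and analysts blinded, so a single analysis fixed in advance is one of its main protections against selective reporting. If the analyst may take whichever result is favourable, the type I error exceeds the nominal level.

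The heading adds a second problem. Taken at face value, it announces a comparison of the arms on all four efficacy scales before the trial ends, with no error control. Taken as a misplaced label, it leaves {21b} silent on whether any interim analysis is planned, and puts a second set of final-analysis methods beside those in {20a}.

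The ANOVA has its own weakness. Week 0 is the baseline score, taken before allocation and used to judge eligibility, so it cannot carry a treatment effect. Change across time points within patients is also not the between-arm question of a superiority trial.

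**Working it through.** **The plan's own figure.** The article states no overall type I error for this set of analyses, so there is none to reproduce. Section {14} gives the level as one-sided 5% in words and as α = 0.025 in symbols. The figures below use two-sided 5% unless stated otherwise.

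**Step 1: the sections side by side.**

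| FMA change is | {20a} | {21b} | Conflict |
|---|---|---|---|
| Normal | t test | Mann-Whitney | Yes |
| Not normal | Rank-sum | Mann-Whitney (the same test) | No |
| Either | – | Repeated-measures ANOVA, deciding term not named | Additional route |

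**Step 2: what free choice costs.** Trials were simulated with no treatment effect. From the document: 86 per arm and five visits. Assumed: the correlation between visits, the error distribution, and a Shapiro-Wilk check as the normality gate in {20a}. Counted: the share of trials in which at least one permitted test has p < 0.05.

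| Permitted analyses | At least one rejection |
|---|---|
| Any single test alone | 4.4–5.4% |
| {20a} test or Mann-Whitney | 5.0–5.9% |
| The same, plus ANOVA group-by-time | 8.3–9.4% |

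These ranges cover equal correlations of 0.5 and 0.8 with normal and skewed errors, 8,000 runs each. With correlation that decays over visits (AR(1), 0.7) and a Greenhouse-Geisser correction, the t test, Mann-Whitney and group-by-time term together give 7.2%. The range for that set is therefore roughly 7–9%, and it depends on the assumed correlation pattern. Nearly all of the excess comes from the ANOVA term. The choice between t and Mann-Whitney adds at most about one percentage point.

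**Step 3: if the heading is literal.** Suppose one unadjusted look at half the information, followed by the final test, both at |z| > 1.96. The two statistics have correlation √0.5 ≈ 0.707 under the null.

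P(|Z₁| > 1.96 or |Z₂| > 1.96) ≈ 8.3% by bivariate normal integration (8.4% by simulation).

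At one-sided 0.025, the level given in symbols in {14}, the same calculation gives about 4.1% against a nominal 2.5%.

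**Step 4: week 0 as an outcome time.** If change scores are analysed, the week 0 value is zero for every patient. If raw scores are analysed, the expected arm difference at week 0 is zero by randomisation. With a constant difference d at the four later visits, the ANOVA group effect then estimates (0 + 4d)/5 = 0.8d, which is diluted by a fifth. The time effect pools both arms and does not estimate the treatment effect at all.

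**Step 5: what baseline adjustment gains.** With equal variances and correlation ρ between baseline and 3-month FMA, the variance of the adjusted difference relative to the change-score difference is (1 − ρ²)/[2(1 − ρ)] = (1 + ρ)/2. That is 0.75 at ρ = 0.5 and 0.90 at ρ = 0.8 (ρ assumed).

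**The case against.** The strongest defence is that little is really in conflict. Mann-Whitney and the rank-sum test are one test under two names, so the sections agree whenever the data are not normal. On its wording, {21b} uses Mann-Whitney to compare the arms and the ANOVA to describe the course over time, so the ANOVA need not be a rival test of the primary outcome. The variable and the visit are fixed in {14}. This is a journal article, and naming the deciding model is commonly left to an analysis plan that is not shown. Including baseline as a level of a repeated-measures ANOVA is common practice, and MAS, a secondary outcome, also receives a rank test.

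Most of this stands, and it limits the weight of the point. What remains is that the printed text gives two different rules for normal data and files one of them under a heading that does not fit. An unseen plan would still have to depart from one of the two sections.

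Two stronger readings are tempting. A reader might infer that the arms will be compared on four scales at an unadjusted interim look. The text does not support this: it describes no look, and its content runs from baseline to week 12 and adverse events, which fits a final analysis under the wrong template heading. A reader might also infer that three rival tests of the primary outcome are on offer. That needs an ANOVA group or group-by-time term, and {21b} names neither.

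**Conclusion.** The inconsistency is real and modest, and it should be fixed. The direct conflict between {20a} and {21b} applies only when FMA change is normal, and is worth about 5.0–5.9% type I error if either test may be chosen. The figure of roughly 7–9% rests on three assumptions: that a group-by-time term may also be picked, that the visit correlations are those assumed, and that the level is two-sided 5%. The 8.3% for an interim look (about 4.1% at one-sided 0.025) is conditional on a literal heading, which the content of the section makes unlikely.

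The endpoint is not open to choice. What is open is the test that decides it, and whether an interim efficacy analysis exists. Apart from the size of any inflation, the ANOVA as described counts a pre-randomisation score as an outcome, and its time effect does not answer the between-arm question.

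**What to change.** 1. In {21b}, state that no interim efficacy analysis is planned. If one is intended, give its timing and alpha rule. Move the methods now listed there to {20a}.
2. Name one primary analysis: the between-arm difference in FMA at 3 months adjusted for baseline FMA. This can be an ANCOVA, or a mixed model over weeks 2 to 12 with baseline as covariate and the week-12 contrast as primary.
3. Label Mann-Whitney on the FMA change as a sensitivity analysis and the time-course analysis as supportive. Baseline should enter as a covariate, not as an outcome time.
4. Use a rank or ordinal method for the MAS grade.

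The cost is a change of text and slightly more analysis work. Baseline FMA is already collected, so no new data, visits or patients are needed.

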### Methods for additional analyses (e.g. subgroup analyses) {20b}

Subgroup analysis will be conducted according to the severity of impairment in the limbs and age (e.g. NIHSS 5–15, NIHSS 15–20, NIHSS 20–22; age 35–45, age 45–65, age 65–80, respectively).

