## Introduction

### Background and rationale {6a}

In recent years, the incidence of stroke and the associated mortality rate in China have increased [1]. Epidemiological findings show that the age-standardised prevalence, incidence and mortality rates were 1114.8 per 100,000, 246.8 per 100,000 and 114.8 per 100,000, respectively, in 2013 [2]. Ischaemic stroke accounts for 69.6–77.8% of all strokes [2]. China ranks first amongst all countries in terms of the DALYs (disability-adjusted life years) resulting from stroke [1]. Stroke has become the most common and major cause of disability [3, 4]. Approximately 70–80% of the existing stroke patients have lost, to some extent, their ability to work [5]. Hemiplegia, one of the most common sequelae after stroke, directly affects the quality of work and life of patients and imposes a heavy economic burden on society and families [6].

Evidence-based medicine (EBM) has confirmed that rehabilitation training is the most effective treatment for decreasing the disability rate [7, 8]. In modern medicine, the conventional treatments also include exercise therapy [9], traditional Chinese medicine (TCM) exercise therapy [10, 11], medicine [12], acupuncture [12, 13], transcranial magnetic stimulation (TMS) [14–16], mirror therapy [17] and music-supported therapy [18]. In China, acupuncture is one of the most common physical therapies performed to treat stroke-associated hemiplegia and can reduce muscle tension in patients with spastic hemiplegia after stroke [19, 20]. Acupuncture is known to yield better results when the intervention is implemented earlier [21]. However, due to the complexity of patients’ conditions, the processes for selecting safe and effective acupuncture points as well as performing manipulation according to the actual patient conditions need to be explored further.

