## Interventions

### Explanation for the choice of comparators {6b}

In China, stroke patients are often treated with acupuncture. Thus, the patients can easily determine whether fake acupuncture is used. Therefore, we decided to perform standard procedure acupuncture rather than sham acupuncture for the control group.

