## Assignment of interventions: allocation

### Sequence generation {16a}

Commonly used factors for patient stratification include age, sex, body mass index (BMI), smoking habits, and alcohol consumption habits. In this study, the patients are expected to have a large age gap. Therefore, we have chosen age as the blocking factor. All participants will be randomly assigned to one of two groups (‘hand and foot acupuncture with twelve needles’ group and routine acupuncture group) in a 1:1 ratio. The generation and allocation of a random sequence for group assignment will be conducted by the World Federation of Chinese Medicine Societies in China. A block randomisation method (with a block size of four) will be used to generate the random allocation sequence; opaque sealed envelopes containing the predetermined computer-generated numbers will be used to ensure allocation concealment.

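### The stated tests of FMA change are unadjusted and use time since stroke onset only descriptively, although the rationale says timing matters; adjusting for it is a free gain in precision

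*Protocol article*

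**What the plan says.** Background and rationale {6a} states: "Acupuncture is known to yield better results when the intervention is implemented earlier". Inclusion criterion C admits patients whose stroke was between 2 weeks and 3 months ago. Sample size {14} takes the change in FMA from baseline to 3 months as the primary efficacy parameter.

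The analyses are named in three places.

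- Statistical methods {20a}: "An independent *t* test or rank-sum test will be performed to assess the differences between the two groups".
- Interim analyses {21b}: "Mann-Whitney U test will be used to analyse value changes of FMA, NIHSS, MAS, and BI scores among the groups", and "Repeated measures analysis of variance (ANOVA) will be used to analyse value changes of FMA, NIHSS, MAS, and BI scores across five testing time points".
- Additional analyses {20b}: "Subgroup analysis will be conducted according to the severity of impairment in the limbs and age", with bands of NIHSS and of age.

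None of these names a covariate. The only mention of disease duration in the analysis sections is in the list of baseline characteristics to be described, "such as gender, age, disease course, and stroke risk factors". Randomisation uses age alone: "Therefore, we have chosen age as the blocking factor". The comparator is also acupuncture: "we decided to perform standard procedure acupuncture rather than sham acupuncture for the control group".

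**The concern.** Patients may enter anywhere from 2 to about 13 weeks after onset, and each is then followed for about 12 weeks. If recovery slows with time, early and late entrants have different expected FMA gains whichever technique they receive. The protocol's own remark about early treatment points the same way. The stated tests leave any such variation in the error term, although the value that would explain it is already in hand: it is needed to check eligibility and is to be described at baseline.

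What is at stake is precision. Both arms receive active acupuncture five times a week for 4 weeks on top of rehabilitation, so the true difference between them may be modest.

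**Working it through.** **1. Does onset time enter any comparison?**

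| Place | Factor used | Time since onset? |
|---|---|---|
| Sequence generation {16a} | age | no |
| Statistical methods {20a} | none (t or rank-sum test) | no |
| Interim analyses {21b}, tests | none named (Mann-Whitney, repeated measures ANOVA) | no |
| Interim analyses {21b}, baseline table | disease course | description only |
| Additional analyses {20b} | NIHSS, age | no |

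**2. What does the rationale imply for this contrast?** The sentence in {6a} is about acupuncture in general. Both arms receive acupuncture, so it implies a better response to early treatment in both. That describes a prognostic factor. No section says that timing changes the difference between the twelve-needle and the routine technique.

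**3. The plan's own sample size.** Inputs from {14}: means 25.82 and 12.11 (difference 13.71), SD 4, α = 0.025, power 0.80.

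n per group = 2 × (1.96 + 0.84)² × 4² / 13.71² = 1.3, rounded up to 2 (normal approximation).

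The stated 86 does not reproduce. At the stated difference and SD, 86 per group gives power of 100% to rounding, with or without a covariate. That discrepancy is a separate matter. Here I take 86 per group as the intended evaluable number and ask what difference it detects with 80% power:

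4 × (1.96 + 0.84) × √(2/86) = 4 × 0.427 = 1.71 FMA points.

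**4. Gain from adjusting for onset time.** Let R² be the share of variance in FMA change that onset time explains. The documents give no value, so 2% to 30% is assumed. The residual SD becomes 4 × √(1 − R²). Power at the 1.71-point difference is Φ(2.80 / √(1 − R²) − 1.96), and the number per group for 80% power is 86 × (1 − R²), rounded up.

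| Assumed R² | Residual SD | Power with 86 per group | n per group for 80% |
|---|---|---|---|
| 0 | 4.00 | 80.0% | 86 |
| 0.02 | 3.96 | 80.8% | 85 |
| 0.05 | 3.90 | 82.0% | 82 |
| 0.10 | 3.79 | 84.0% | 78 |
| 0.20 | 3.58 | 87.9% | 69 |
| 0.30 | 3.35 | 91.8% | 61 |

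The gain is about 1 to 12 percentage points. The SD cancels from the power column, so doubt about the value of 4 does not affect it. The table counts onset time only. Once baseline FMA is in the model, the relevant R² is the share of the remaining variance that onset time explains.

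**5. Power of an interaction test.** Split the 86 per group at early versus late entry, 43 in each of four cells. The standard error of the difference between the two treatment effects is 4 × √(4/43) = 1.22. For an interaction of 1.71 points at two-sided 5%: Φ(1.71/1.22 − 1.96) = Φ(−0.56) = 29%. About 3.4 points, twice the main-effect difference, is needed for 80%.

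**The case against.** The case against has several parts.

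- **No error of validity.** Randomisation balances onset time on average, so the unadjusted comparison is unbiased. This stands. A reader might infer that a wide entry window with no adjustment biases the result; nothing in the documents supports that.
- **Not a stated effect modifier.** A reader might infer from {6a} that the protocol names earliness as the main modifier of its treatment effect and then fails to test it. The text does not go that far. It speaks of acupuncture in general, both arms receive it, and no ranking of modifiers is given. This stands.
- **Age is not an arbitrary choice.** A reader might object that age bands are analysed without a reason. Section {16a} gives one, a wide expected age range, and makes age the randomisation factor. Analysing by that factor is ordinary. This stands.
- **The size is unknown.** The documents contain no recovery curve, no distribution of entry times and no R². A large ratio of gains between the earliest and latest entrants can be produced by choosing a steep curve, but that would be assumption. This stands, and is why only a range is given.
- **Covariates may be left to an analysis plan that is not shown.** This stands only in part. The article is not silent: it names its between-group tests, and neither a t test nor a rank-sum test can carry a covariate. Adjustment would therefore change a stated method, not merely fill in a detail.
- **The change is more than one added term.** Correct: the primary method is replaced by a linear model. It is still a standard analysis on data already collected.

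**Conclusion.** The point holds as a matter of efficiency. The stated comparison of FMA change leaves out a recorded baseline value that the protocol's own rationale makes a likely predictor of outcome in both arms. The comparison is valid but may be less precise than it could be. The possible gain is about 1 to 12 points of power at the difference detectable with 80% power, or a reduction from 86 to between 85 and 61 per group. This rests on an assumed R² of 2% to 30%, on 86 evaluable per group, and on a one-sided 0.025 level as in the parameter list of {14}. It also assumes that disease course means time since onset. If the true difference were as large as the 13.71 points in {14} with SD 4, the gain would be immaterial; it matters if two active acupuncture techniques differ by much less.

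The omission of onset time from the subgroup list is secondary. It leaves open an exploratory question that this sample is unlikely to settle.

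**What to change.** In Statistical methods {20a}, make the primary comparison of FMA change from baseline to 3 months a linear model (ANCOVA) with treatment, baseline FMA and days from stroke onset to enrolment (continuous) as prespecified covariates. It replaces the unadjusted t or rank-sum test as the primary method. State it before any unblinded look at the data, so that the covariates cannot be chosen after the results are seen.

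Optionally, add a treatment by time-since-onset interaction, with onset time continuous, to Additional analyses {20b}. Label it exploratory and say that its power is low.

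The cost is a change to the text of the plan and to the analysis program. Onset time is already needed for eligibility and baseline FMA is already scored, so no new visits, data items or participants are required.

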### Methods in analysis to handle protocol non-adherence and any statistical methods to handle missing data {20c}

If data are missing, the missing data field will be populated with the value of the last measurement.

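### Last observation carried forward is the only missing-data rule stated, in patients expected to keep improving, and it can bias the 3-month FMA contrast in either direction

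*Protocol article*

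**What the plan says.** The protocol's section on non-adherence and missing data (item 20c) consists of one sentence, which provides that in the event of missing data "the missing data field will be populated with the value of the last measurement". It attaches no condition and names no other method.

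The Sample size section (item 14) defines the endpoint to which the rule applies: "The primary efficacy parameter is the change in the FMA score from baseline to 3 months after the treatment". I take this as the 3-month visit, the last in the schedule. The same section assumes that the FMA score "of the control group (rehabilitation treatment) will increase by 12.11 points", and that the score of the treatment group ("scalp acupuncture combination rehabilitation treatment) will increase by 25.82 points". It adds: "The FMA average standard deviation is expected to be approximately 4". Enrolment is set at 104 per group after an allowance for 20% dropout.

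Elsewhere, the inclusion criteria admit patients 2 weeks to 3 months after onset. Assessments are at baseline, 2 weeks and 1, 2 and 3 months. Participants and researchers are not blinded (item 17a).

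**The concern.** LOCF treats a participant's FMA score as fixed from the last visit attended. The protocol plans on the opposite, since both assumed gains are well above zero over the follow-up. Someone lost before the 2-week visit would be recorded as having gained nothing at 3 months, and someone lost later would be recorded with only part of the gain.

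The error grows with the proportion lost and with the gain still to come, so it need not be the same in the two arms. If the arms gain about equally, the arm that loses more patients is penalised. If they gain differently and lose equally, the contrast is pulled towards zero. LOCF therefore cannot be defended as reliably conservative. At stake is the primary comparison, with about one participant in five expected to be lost: a false claim of superiority is possible, and so is an understated true effect.

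**Working it through.** **Inputs from the protocol.** Gains g = 12.11 and 25.82 points (difference 13.71); SD 4; 104 per arm; overall dropout 20%.

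**Assumptions not in the protocol.** Dropout q by arm; the share f of the 3-month gain already reached at the last visit attended, the same in both arms; dropouts would have gained as much as completers; carried changes have SD 4; normal test at two-sided 5%, so 2.5% in each direction. The protocol gives no FMA trajectory, so f is shown over a range.

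**The plan's own figure.** n per group = 2(1.96 + 0.84)² × 4² / 13.71² = 1.34, rounded up to 2, not the stated 86. The section's two descriptions of the significance level ("Considering a one-sided 5% significance level, 80% power and the above data", then α = 0.025) both give 2. This is a separate matter. It counts here only because the stated 80% power cannot serve as a baseline.

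**Formulas under LOCF.**
- Mean recorded change in an arm = g[1 − q(1 − f)].
- Variance in an arm = 16 + q(1 − q)[(1 − f)g]².
- Bias of the contrast (treatment minus control) = −(1 − f)(g_T q_T − g_C q_C).

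**Equal 20% dropout, planned gains.** Bias = −(1 − f) × 0.20 × 13.71 = −2.74(1 − f). This is −2.74, −2.06, −1.37 and −0.69 points at f = 0, 0.25, 0.5 and 0.75, or 20% down to 5% of the planned contrast.

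**Unequal dropout, planned gains.**
- Treatment 10%, control 30%: −(1 − f)(2.58 − 3.63), which is +1.05 points at f = 0 and +0.26 at f = 0.75.
- Treatment 30%, control 10%: −(1 − f)(7.75 − 1.21), which is −6.54 and −1.63 points.
- The bias is zero when q_T/q_C = 12.11/25.82 = 0.47.

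**No true effect, both arms gain 12.11, dropout 15% versus 25%.** Spurious difference = (1 − f) × 0.10 × 12.11. At f = 0 the variances are 16 + 0.15 × 0.85 × 12.11² = 34.70 and 16 + 0.25 × 0.75 × 12.11² = 43.50. The SE is √(78.20/104) = 0.867, and the chance of favouring the arm with less dropout is P(Z > 1.96 − 1.211/0.867) = 28.7%.

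| f | Spurious difference | SE | Chance of falsely favouring the arm with less dropout |
|---|---|---|---|
| 0 | 1.21 | 0.867 | 28.7% |
| 0.25 | 0.91 | 0.747 | 22.8% |
| 0.5 | 0.61 | 0.647 | 15.3% |
| 0.75 | 0.30 | 0.579 | 7.5% |
| 0.9 | 0.12 | 0.559 | 4.1% |

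With equal dropout and equal gains there is no bias, and the rate stays at 2.5% in each direction.

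**Power, equal 20% dropout.** On the planned inputs the worst case (f = 0) is a difference of 10.97 with SE 1.249, a ratio of 8.8, so power is above 99.9%. For a small effect, take 1.71 points, the difference that 86 per arm would detect with 80% power at SD 4. LOCF power is then 32%, 47%, 64%, 79.5% and 85% at f = 0, 0.25, 0.5, 0.75 and 0.9. For 83 completers per arm (104 × 0.8 = 83.2) it is 78.6%.

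**The case against.** The strongest reply is that the size of the bias rests on inputs the protocol does not supply. This is correct, and it limits what can be claimed.

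- **Dropout by arm is assumed.** Both arms receive active acupuncture on the same schedule, so the open-label design is a weaker driver of unequal loss than it would be against sham or no treatment. The 15%/25% split is only an illustration.
- **Timing is assumed.** Treatment ends at 4 weeks and visits continue to 3 months, so late dropout is plausible, and late dropout makes the bias small.
- **The gains are borrowed.** They come from rehabilitation alone and from scalp acupuncture plus rehabilitation, not from this trial's two arms.
- **The SD matters.** If it were about 32, the value at which 86 per group would fit a 13.71-point difference, the false-favouring rate in the illustration would be only 4.6% (f = 0) to 2.9% (f = 0.75). The bias in points would be unchanged.
- **A sensitivity analysis may stand in a statistical analysis plan that is not shown.** The point therefore rests on the rule that the protocol fixes, not on something absent.

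Three stronger readings are tempting, and the protocol does not support them. A reader might infer that any difference in dropout biases the contrast; with the planned gains the errors cancel when treatment dropout is about 0.47 times control dropout, although that would be a coincidence. A reader might infer that LOCF always costs power; on the planned inputs it does not, and with late dropout LOCF matches or exceeds completers because all 104 per arm are kept. A reader might infer that a pre-event score is carried past a recurrent stroke; the rule acts only on missing values, and nothing says that FMA assessment stops after a recurrence.

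None of this supplies a reason to expect scores to stay fixed after dropout.

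**Conclusion.** The point stands as a criticism of the rule. LOCF, the only method stated, conflicts with the improvement the protocol plans on, and it can move the primary contrast in either direction.

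Under equal 20% dropout and the planned gains, the contrast shrinks by about 2.7 to 0.7 of 13.71 points as the share of gain reached at dropout goes from 0 to 75%. With no true effect and an assumed 15%/25% split, the spurious difference is 1.2 to 0.3 points, and the chance of falsely favouring the arm with less dropout is about 29% to 8% rather than 2.5%. That range assumes a gain of 12.11 in both arms, SD 4 and 104 per arm. It approaches nominal when dropout is late and is much smaller if the SD is far above 4.

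Loss of power is conditional: it needs early dropout and a small true difference. The existence of the bias is well supported; its size in this trial cannot be known from the protocol.

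**What to change.** For the primary analysis, replace LOCF with a likelihood-based mixed model for repeated measures on all randomised participants. Use the observed FMA scores at weeks 2, 4, 8 and 12, with group, visit, group-by-visit, baseline FMA and age as terms, and take the week-12 group difference as the primary estimate. Age should enter in the form used in the randomisation. The section on sequence generation names age as the blocking factor but gives no cut-points, so that form must be written down.

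Add one sensitivity analysis by delta-adjusted or reference-based multiple imputation. Keep LOCF, if at all, as supportive only.

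The cost is analysis wording and slightly more programming. No new data are needed: the visits are already scheduled, and the protocol already plans a repeated-measures analysis over the five time points. The drawback is that the primary model relies on data being missing at random, an assumption that the sensitivity analysis is there to test.
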